# STUDY SYNOPSIS

| Study Title | Evaluating the effect of pulsed near infrared transcranial and intranasal photobiomodulation on real-time EEG signals in older adults at rest |
| --- | --- |
| Study Objective | To evaluate whether pulsed near infrared transcranial and intranasal photobiomodulation produces a reliable effect on neural activity in older adults. |
| Methodology | Double-blind, prospective, crossover |
| Study Duration | Two session evaluation |
| Number of Subjects | Maximum of 20 older adults |
| Major Inclusion/Exclusion Criteria | - 60 years of age or older - No current major psychiatric or neurologic disease - No history of stroke or seizures - All other medical conditions controlled by stable therapy |
| Study Intervention and Planned Use | The experimental intervention will be delivered using the Vielight Neuro Gamma device. The device uses 5 light emitting diodes (810nm wavelength). Four diodes provide near-infrared energy transcranially, while the last does so intranasally, all targeting regions of the Default Mode Network. No significant heat is generated, allowing for a sham device which will be indistinguishable from the intervention to both the subjects and EEG technician. Devices will be utilized concurrently with EEG recording of subject at rest. The devices will be used in a randomized crossover design within the single study visit with the same EEG recordings to be obtained under both sham and active conditions. |
| Study Procedures | 1. Informed Consent 2. Eligibility Assessment 3. First EEG Recording 4. One week washout period 5. Second EEG Recording |
| Primary Endpoint | Change from baseline in overall power spectral density between active and sham session |
| Statistical Methodology | Repeated measures ANOVA with treatment as within subject measure |

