- Study staff will record any relevant subject details (physical characteristics and demographics) in the Case Report Form. These include but are not limited to: the Subject’s date of birth (YYYY-MM-DD), sex, weight, height, etc.
- Study staff will place the saline-rinsed EEG electrode cap on the subject and may apply additional saline to individual electrode locations in order to ensure good conductivity
- Once the electrode cap is producing reliable readings, the subject will be asked to remain still and quiet with their eyes closed for an initial 10 min Rest-EEG recording
- At the completion of the 10 min recording, study staff will then place the Vielight Neuro Gamma device or Sham device on the subject, as shown in Figure 2 above.
- Study staff may then re-apply additional saline to individual electrode locations in order to ensure good conductivity
- Once the electrode cap is producing reliable readings, the subject will be asked again to remain still and quiet with their eyes closed for a 20 min Rest-EEG recording
- At the completion of the 20 min recording, study staff will then remove the Vielight Neuro Gamma device or Sham device and again re-apply additional saline to individual electrode locations in order to ensure good conductivity
- Once the electrode cap is producing reliable readings, the subject will be asked to remain still and quiet with their eyes closed for a final 10 min Rest-EEG recording

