# STATISTICAL PLAN AND METHODS

## Planned Analysis

The primary endpoint for this study will be the change from baseline in overall power spectral density between active and sham session. To statistically determine a significant difference a repeated measures ANOVA with treatment as the within-subject measure will be utilized.

Additional exploratory analysis of a variety of measures obtained from the EEG recording will be conducted post-hoc.

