## Primary Endpoint Analysis: Sample Size Selection

The sample size of the study was chosen based on a review of the literature for exploratory EEG studies of novel neurotechnologies. Utilizing a sample size of 20 for this initial study will allow us to best estimate effects sizes of critical measures to be examined in follow-up confirmatory studies.

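### The primary analysis subtracts each session's baseline with a fixed slope of 1; estimating the slope would probably be more precise at 20 subjects, by an amount set by a correlation the protocol does not give

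*Protocol*

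**What the plan says.** Section 6.1 (Planned Analysis) states: "The primary endpoint for this study will be the change from baseline in overall power spectral density between active and sham session". The synopsis words the endpoint in the same way: "Change from baseline in overall power spectral density between active and sham session". For the test, Section 6.1 says that "a repeated measures ANOVA with treatment as the within-subject measure will be utilized". No baseline covariate and no period or sequence term is named.

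Section 4.3 (Study Visit Procedures, Part C) supplies the baseline. Before any device is placed, "the subject will be asked to remain still and quiet with their eyes closed for an initial 10 min Rest-EEG recording". The second visit repeats Part C, so each subject has a baseline EEG under both conditions.

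The synopsis limits enrolment to "Maximum of 20 older adults". Section 6.2 gives the basis for that number: "The sample size of the study was chosen based on a review of the literature for exploratory EEG studies of novel neurotechnologies". It gives the aim as well: "Utilizing a sample size of 20 for this initial study will allow us to best estimate effects sizes of critical measures", for use in later confirmatory studies.

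**The concern.** A change score sets the coefficient of the baseline to exactly 1. In a parallel-group trial the usual reason for subtracting a baseline is to remove stable differences between subjects. In a crossover those differences already cancel in the active-minus-sham comparison. What remains is how far a subject's session-to-session fluctuation at baseline carries over into the later recording of the same session. If it carries over only partly, subtracting the whole baseline adds noise.

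Precision is the stated purpose of the sample size here. N is capped, no power calculation supports it, and the trial is meant to supply effect sizes for later studies. A noisier estimator gives a wider interval and a less reliable planning figure, although the data for a better one are already collected.

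**Working it through.** **The plan's own figure.** N = 20 cannot be reproduced: the protocol states no alpha, power, effect size or standard deviation. For context only, a paired t-test with 20 subjects at an assumed two-sided 5% level has 80% power for a standardised paired effect of 0.66.

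**Set-up.** For each subject let DX be the active-minus-sham difference in baseline power and DY the same difference in the analysed recording. Let r be the correlation of DX and DY. It is not the raw correlation between baseline and later power, which stable subject levels would inflate. Assumptions, none of them in the protocol: normality, equal variances of DX and DY (set to 1), and r over a range.

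**Variance per subject.**
- Change score, DY − DX: 2(1 − r)
- Baseline-adjusted, slope known: 1 − r²
- Baseline ignored, DY alone: 1

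The large-sample ratio adjusted/change is (1 − r²) / [2(1 − r)] = (1 + r)/2. The change score is also less precise than ignoring the baseline when 2(1 − r) > 1, that is, when r < 0.5.

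**Cost of estimating the slope at n = 20.** Multiply by 1 + 1/(n − 3) = 18/17 = 1.059 with no period term, or by 1 + 1/(n − 4) = 17/16 = 1.0625 with one. The simulation used 40,000 trials per value of r, 10 subjects per sequence and a period term in both models. The effect was set so that the change score had about 80% power.

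| r | (1 + r)/2 | × 18/17 | × 17/16 | Simulated ratio | Simulated power, change → adjusted |
| --- | --- | --- | --- | --- | --- |
| 0.3 | 0.65 | 0.69 | 0.69 | 0.69 | 80% → 92% |
| 0.5 | 0.75 | 0.79 | 0.80 | 0.79 | 80% → 88% |
| 0.7 | 0.85 | 0.90 | 0.90 | 0.91 | 80% → 83% |
| 0.8 | 0.90 | 0.95 | 0.96 | 0.96 | 80% → 82% |
| 0.9 | 0.95 | 1.01 | 1.01 | 1.02 | 80% → 79% |
| 0.95 | 0.975 | 1.03 | 1.04 | 1.04 | 80% → 78% |

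**Break-even.** Without a period term, (1 + r)/2 × 18/17 = 1 gives r = 2 × 17/18 − 1 = 0.89. With one, r = 2 × 16/17 − 1 = 0.88. As r approaches 1 the ratio approaches 18/17 or 17/16, so the loss is at most about 6%.

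**In subjects.** To match 20 adjusted subjects, the change score would need 20/0.797 = 25 at r = 0.5, 20/0.903 = 22 at r = 0.7 and 20/0.956 = 21 at r = 0.8 (period term included).

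**Unequal variances.** Let k be the SD of DY divided by the SD of DX. The large-sample ratio becomes k²(1 − r²) / [k²(1 − r²) + (1 − rk)²]. At r = 0.7:
- k = 1.2: 0.7344 / (0.7344 + 0.0256) = 0.97, and × 17/16 = 1.03, so no gain.
- k = 0.8: 0.3264 / (0.3264 + 0.1936) = 0.63, and × 17/16 = 0.67, a larger gain than with equal variances.

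**The case against.** The strongest reply is that nothing here is wrong. A within-subject comparison of changes from baseline is coherent and standard, and it is unbiased if order is randomised. That stands: this is a point about efficiency. A reader might infer that the endpoint is biased or invalid, and the documents do not support that. If order were not randomised, as the Study Design section states, both estimators would face that problem.

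A second reply is that a change-score endpoint does not rule out adjustment. That also stands. Regressing DY − DX on DX gives the same intercept as regressing DY on DX, so the endpoint wording can stay. A statistical analysis plan that is not shown could add the covariate. The protocol does, however, state its primary model, and that model names treatment alone.

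A third reply is that r could be high. Both recordings come from one sitting, with the subject in the same resting, eyes-closed state, and no removal of the cap between them is described. Against this, Part C places the device on the head and allows saline to be re-applied before the next recording, and saline is applied again after the device is removed. The documents cannot settle r. It would therefore go too far to say that the plan certainly wastes precision: at r = 0.8 the gain is only 4 to 5%, and by about 0.88 there is none.

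**Conclusion.** The point holds as a conditional efficiency improvement. As written, the primary analysis fixes the baseline slope at 1 although a baseline is recorded in both sessions. At 20 subjects, estimating the slope would lower the variance by about 31%, 21%, 10% and 5% at r = 0.3, 0.5, 0.7 and 0.8. From about r = 0.88 it would gain nothing, and above that it would cost at most about 6%. These figures rest on assumed values of r, normality and equal variances of the two differences; a modest departure from equal variances can remove the gain or enlarge it.

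The case for acting although r is unknown is the asymmetry under equal variances: a small, bounded loss if r is very high, against a material gain if it is low or moderate. The estimated slope would also be useful in planning the follow-up studies that Section 6.2 has in view.

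**What to change.** In Section 6.1 and the synopsis, keep the change-from-baseline wording and the measurement scale, and add the within-subject (active-minus-sham) baseline difference as a covariate. Equivalently, regress each subject's active-minus-sham difference in the analysed recording on the baseline difference. Report the intercept, which is the treatment effect at zero baseline difference, with a 95% confidence interval. Keep the unadjusted change as a sensitivity analysis.

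If both orders are used, add a sequence term coded −1/+1. This has to wait until the synopsis, which describes a randomised crossover, is reconciled with the Study Design section, which calls the study non-randomised.

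The cost is a couple of sentences and no new data. The treatment-only paired analysis leaves 20 − 1 = 19 residual degrees of freedom; the slope takes one (18 left) and the sequence term, if added, a second (17 left). If r turns out very high, a few percent of variance is lost.

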# INTRODUCTION

## Study Rationale & Background

Photobiomodulation (PBM) involves the use of low levels of red or near-infrared (NIR) light to either stimulate or inhibit biological cells and tissues via a photochemical mechanism. Transcranial PBM (tPBM) is used to target the delivery of light energy to the brain. It is associated with increased cerebral blood flow, oxygen availability and consumption, adenoside triphophosphate (ATP) production, and improved mitochondrial activity. However, there are questions as to whether near infrared light is capable of penetrating the skull and/or nasal mucosa to reach and produce reliable effects in the brain. The aim of current study is to utilize electroencephalography (EEG) as a method to measure, in real time, the effects of pulsed near infrared transcranial and intranasal photobiomodulation on neural activity.

## Study Device: Vielight Neuro Gamma

The Vielight Neuro Gamma device is a portable, wearable, low-level light delivery device that administers near-infrared light to the brain trans-cranially and intra-nasally and is intended to enhance mental acuity as part of general wellness. The device, shown below, consists of a controller (1), a Nasal Applicator (2), and a Head Set (3).

[figure not shown]

Figure 1. Vielight Neuro Gamma device

The Vielight Neuro Gamma delivers painless, non-invasive, non-thermal, non-laser, pulsed (40 Hz; 50% duty cycle), near-infrared light (810 nm wavelength) through 5 non-laser light emitting diodes (LEDs) over a 20 minute session. The device is powered by three rechargeable NiMH batteries. As shown below, one of the Vielight Neuro Gamma LEDs is placed inside the nose for intranasal transmission of light energy and the remaining four LEDs are positioned over the skull for transcranial transmission.

| [figure not shown][figure not shown]  Figure 2. Placement of Vielight Neuro Gamma device |
| --- |

##

## Study Objective

In order to effectively test the capability of pulsed near infrared transcranial and intranasal photobiomodulation to affect neural activity, EEGs using an active device must be compared to sham device EEGs in 20 subjects. This will allow us to reasonably calculate whether there is a significant difference in power spectral density as well as examine other relevant outcomes post-hoc.

## Study Design

This is a non-randomized prospective experimental study.

Study Procedures are as follows:

1. Informed Consent
2. Eligibility Assessment
3. First EEG Recording
4. One week washout period
5. Second EEG Recording

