**SECOND STUDY VISIT**

The second study visit will be a replication of Part C of the first visit. At the conclusion of the visit, the subject will be provided financial compensation of $100 CAD for the study.

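### The protocol calls the trial both non-randomized and a randomized crossover and gives no rule for session order; if every subject gets the same order, device and session cannot be separated

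*Protocol*

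**What the plan says.** The protocol describes the allocation of session order in two incompatible ways.

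- Study Design: "This is a non-randomized prospective experimental study".
- Synopsis, study intervention row: "The devices will be used in a randomized crossover design within the single study visit".
- Synopsis, methodology row: "Double-blind, prospective, crossover". Randomization is not mentioned there.

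The visit procedures (Section 4.3) do not settle it. In Part C of the first visit, "study staff will then place the Vielight Neuro Gamma device or Sham device on the subject", with no rule for which device comes first. For the second visit the text is "The second study visit will be a replication of Part C of the first visit", with no statement on order.

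The Synopsis sentence that asserts randomization also places both conditions in one visit. The same Synopsis gives the duration as "Two session evaluation", and Study Design lists a "One week washout period" between two recordings.

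The primary endpoint is the active-versus-sham comparison of change from baseline in overall power spectral density. Planned Analysis (Section 6.1) and the Synopsis test it by repeated measures ANOVA, and treatment is the only within-subject factor they name.

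**The concern.** Whether the order of conditions is randomized is a basic design fact of a crossover, and here it is stated both ways. Staff who follow Study Design could give everyone the same order, or choose the order subject by subject, and still comply with that section.

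A first and a second session can differ for reasons unrelated to light. Each session has its own 10-minute recording before the device is placed, so additive differences in level (a different cap fit, a generally calmer subject) cancel in the change from baseline. Differences in the change itself do not cancel. An example is a subject who grows drowsy faster over 40 minutes of eyes-closed rest (10 + 20 + 10) once the setting is familiar. That remainder can be mistaken for a device effect.

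The stated purpose of the sample size makes this matter: "Utilizing a sample size of 20 for this initial study will allow us to best estimate effects sizes" for later confirmatory studies. An effect size that carries a session effect would be passed on to those studies.

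**Working it through.** The protocol gives no alpha, power, SD or effect size, so there is no figure of its own to reproduce. The check compares the texts, as above, and asks what each reading implies for the primary contrast.

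**Inputs from the protocol.** n = 20 subjects, 2 sessions each; outcome is change from baseline; the model has treatment within subject.

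**Assumptions.** Two-sided alpha 0.05; no true device effect; change from baseline differs between session 2 and session 1 by d, in SDs of the within-subject active-minus-sham difference. The protocol gives no value for d, so a range is shown.

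**Model.** For subject i, write the active-minus-sham difference as D_i = τ + s_i·d + e_i, with SD(e_i) = 1. Here τ is the device effect, s_i = +1 if active comes second and −1 if it comes first.

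**1. Can device and session be separated?** The design matrix has 20 subject columns, one period column and one treatment column, 22 in all.

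- Same order for all: rank 21 of 22. Given the subject columns, treatment and period are aliased, and no later model can separate them.
- Mixed order (checked at 12/8 and 10/10): rank 22 of 22. Both effects are estimable once a period term is included.

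**2. Bias of the treatment-only model.** If k subjects have one order and 20 − k the other, the mean of D_i is shifted, in absolute size, by d·(k − (20 − k))/20.

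| Split | Fraction of session effect in the device estimate |
|---|---|
| 20/0 | (20 − 0)/20 = 1.0 |
| 15/5 | (15 − 5)/20 = 0.5 |
| 12/8 | (12 − 8)/20 = 0.2 |
| 10/10 | 0 |

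**3. Type I error under one fixed order.** With two levels of treatment, the repeated measures ANOVA is a paired t-test on 19 df. Its rejection rate is that of a noncentral t with noncentrality d·√20.

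| d | d·√20 | Rejection rate |
|---|---|---|
| 0 | 0 | 5% |
| 0.1 | 0.447 | 7.1% |
| 0.2 | 0.894 | 13.6% |
| 0.3 | 1.342 | 24.7% |
| 0.5 | 2.236 | 56.5% |
| 0.8 | 3.578 | 92.4% |

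**4. Type I error at an exact 10:10 split** (100,000 simulations per value of d).

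| d | Treatment only | With period term (18 df) |
|---|---|---|
| 0 | 5.0% | 5.0% |
| 0.2 | 4.8% | 5.2% |
| 0.3 | 4.1% | 5.0% |
| 0.5 | 2.8% | 4.8% |
| 0.8 | 1.3% | 5.1% |

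Balance removes the bias. Without a period term, however, the ±d shifts stay in the error variance, and its expected value rises from 1 to 1 + d²·20/19. At d = 0.5 that is 1 + 0.25 × 20/19 = 1.26. The test is then conservative. It returns to about 5% only when period is in the model.

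**The case against.** The strongest reply is that non-randomized is a slip in one sentence. The Synopsis is the only text that speaks to order, and it says randomized. It also claims double blinding, with a sham that neither subject nor EEG technician can tell from the active device, which sits poorly with staff choosing the order. Nothing in the protocol ranks Study Design above the Synopsis. This is a fair argument about intent, but it does not remove the contradiction. The one sentence that asserts randomization also conflicts with the rest of the protocol on the number of visits, so it is weak evidence on its own. Nor can this be left to an analysis plan: the protocol states the design feature both ways, and no analysis can undo a single fixed order.

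A reader might infer three stronger claims that the protocol does not support.

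- *Without randomization the device effect can never be isolated.* That is true only if everyone has the same order. With alternation or any other mixed order, a model with period separates the two effects. What remains is possible allocation bias.
- *All subjects get one order.* No passage says so. It is one of several arrangements that Study Design permits.
- *The blind is broken.* That would require staff or subjects to know the order, which is stated nowhere.

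It is also fair to object that the error rates rest on assumed values of d and on the worst-case order. They show how sensitive the test is, not how large the problem is in this trial. The in-session baseline removes part of what might otherwise be blamed on session.

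The exploratory aim is not a defence, because an effect estimate for planning needs to be free of order bias as much as a test does.

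**Conclusion.** The contradiction on randomization is certain and needs correction before the primary result can be interpreted. Its effect on that result is conditional.

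- **One order for all:** complete aliasing. Type I error is 13.6%, 24.7% or 56.5% at an assumed session difference in change from baseline of 0.2, 0.3 or 0.5 SD.
- **Mixed but not randomized:** without a period term, a fraction of the session effect enters the device estimate (0.5 at 15/5, 0.2 at 12/8, none at 10/10). A period term removes that bias, but not the possibility of allocation bias.
- **Randomized and balanced, with period in the model:** type I error stays near 5%.

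These figures assume two-sided 5%, all 20 subjects with both sessions, and the stated range of d. None of these d values comes from the protocol.

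**What to change.** 1. In Study Design, replace the non-randomized sentence with a statement that the trial is a randomized, double-blind, sham-controlled, two-period crossover. Subjects should be allocated 1:1 to active-then-sham or sham-then-active from a pre-generated list that is concealed from those recording the EEG. Refer to the section by title, because the contents list uses the number 2.1 twice.
2. In Planned Analysis and the Synopsis, add period as a factor in the repeated measures ANOVA. Randomizing the order without this step gives an unbiased but conservative test. The term also covers departures from 10:10.
3. Reconcile the single-visit wording in the Synopsis with the two-visit, one-week schedule given elsewhere.
4. If order has already been assigned without randomization, remove the word randomized from the Synopsis, report how many subjects had each order, and adjust for period if both orders occurred. Describe the effect as confounded with order only if a single order was used.

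The cost is one wording amendment, a 20-line allocation list and one degree of freedom (19 to 18). No subjects or visits are added.

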## Study Endpoints

Detailed information about endpoint calculation is provided in Section 6 Statistical Plan and Methods.

